### Data collection

Demographic data, questionnaires and physical assessments will be recorded by research physiotherapists blinded to group allocation at baseline and 6 months after randomisation. All outcomes will be assessed by research physiotherapists who will be trained in the conduct of the outcome assessment and are unaware of group allocation. Where face-to-face data collection is not possible, Zoom will be used with non-blinded TCs acting as local support under the supervision of the research physiotherapist to ensure safe and accurate data collection. Prior to the follow-up assessments, participants and TCs will be instructed not to inform the assessor of the their group assignment.

All intervention delivery costs including staff and equipment costs and all health service utilisation will be collected during the study period. The health service utilisation, falls and exercise data will be recorded by home care participants in their self-reported exercise diary and falls and health utilisation calendars. This data will be posted back to the research team by our aged care partners at the completion of the trial. In residential aged care this data will be recorded by TCs in the online documentation system. All data will be collected and uploaded into the REDCap database by a blinded member of our research team via auditing the participant’s online medical records and calendars.

All qualitative data will be collected by experienced research assistants using questionnaires and semistructured interviews via zoom. The implementation data collection related to the intervention’s reach, fidelity, dose delivered, adoption, feasibility and exercise adherence measures will be conducted by research assistants via audits of participants’ exercise diaries and physiotherapy notes.

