### Outcomes

All outcomes will be measured in the intervention and control groups at baseline and 6 months after randomisation.

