### Data analysis

The primary analysis will be based on an intention-to-treat approach. The primary effectiveness outcome will be assessed as a change in participants' mobility using the SPPB. It will be treated as a continuous variable. The effect of group allocation on the outcome at 6-month follow-up will be analysed using linear regression models with baseline scores entered into the linear regression model as a covariate. Alternatively, if distributions are overly skewed (on visual inspection of histograms), the change scores (post-pre) will be analysed. The number of falls per person year will be analysed using negative binomial regression models to estimate the between-group difference in fall rates after 6 months with exposure entered as the offset variable.^31^ The other secondary continuous outcomes (five times sit-to-stand test and EQ-5D-5L) will be analysed using regression models with baseline variables as covariates as described for the primary outcome.^31^ Ordinal regression will be used to compare groups on the GAS.

Prespecified subgroup analyses will use interaction terms (group × outcome) in the model to explore whether there is a differential effect of the intervention in residential aged care facilities versus community-dwelling residents and in those with more marked cognitive impairment. Secondary analyses using causal modelling maybe conducted to establish intervention effects in people with greater exercise dose.^32^

Cost-effectiveness will be explored as the cost per extra person avoiding mobility deterioration as defined as an improvement or no change in the 12-point SPPB score between baseline and 6 months. Cost-effectiveness analysis may also be conducted on falls (ratios will be calculated relative to the control group for the incremental cost per fall avoided per person) and the quality-adjusted life year (QALY) gained (calculated from EQ-5D-5L). Bootstrapping will estimate a distribution around costs and health outcomes and calculate the CIs around the incremental cost-effectiveness ratios. The results will be plotted on the cost-effectiveness plane, and as cost-effectiveness acceptability curves. These methods have been used previously when calculating the incremental cost-effectiveness ratios for exercise programmes for older people.^33^

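### The falls model names no baseline covariate; prespecifying one is a cheap gain in precision, but its size cannot be derived from the protocol

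*Protocol article*

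**What the plan says.** The Data analysis section sets covariates outcome by outcome.

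- **Primary outcome (SPPB):** "linear regression models with baseline scores entered into the linear regression model as a covariate".
- **Falls:** a negative binomial model "to estimate the between-group difference in fall rates after 6 months with exposure entered as the offset variable". No further term is named.
- **Sit-to-stand and EQ-5D-5L:** "The other secondary continuous outcomes (five times sit-to-stand test and EQ-5D-5L) will be analysed using regression models with baseline variables as covariates", following the primary model.

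The Abstract draws the same line: baseline adjustment for mobility and the continuous secondary outcomes, then falls separately with no adjustment mentioned.

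On what is measured, the Outcomes section opens with: "All outcomes will be measured in the intervention and control groups at baseline and 6 months after randomisation". Falls are the first of four items under Secondary outcomes. The Data collection section describes how falls are captured: people in home care note them in diaries and calendars that are returned when the trial is complete. In residential care, coaches enter them in the online record. No recall question, look-back period or pre-randomisation recording is described. Physical assessments, which include the SPPB, are made at baseline.

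**The concern.** Fall counts vary widely between people, and someone who fell before randomisation is likely to be more prone to fall afterwards. A baseline variable that captures part of that variation would reduce the residual dispersion and narrow the confidence interval for the rate ratio. The plan takes this benefit for every continuous outcome it models but not for falls, although its own Outcomes statement implies that a baseline falls value is available.

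Precision is at stake, not validity. It matters because falls are likely to be estimated imprecisely in a trial sized on the SPPB, and because the same data may feed the cost per fall avoided. If a covariate is wanted, it has to be fixed before unblinding; chosen later, it would invite doubt about the falls result.

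**Working it through.** **1. The text side by side**

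| Outcome | Model | Baseline term | Baseline value described? |
|---|---|---|---|
| SPPB | linear | baseline score | yes |
| Sit-to-stand, EQ-5D-5L | regression | baseline variables | yes |
| Falls | negative binomial, exposure offset | none named | only through the general Outcomes sentence |

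Either a baseline falls value is collected and not used, or the Outcomes sentence is not accurate for falls.

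**2. Inputs for the size of the gain**

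The protocol gives no figure for the precision of the falls model, so there is none to reproduce. From Sample size: 120 per group and 20% dropout, so 120 × 0.8 = 96 per arm. Follow-up is 0.5 year. Assumed, because the documents give none: 1-3 falls per person-year (control mean μ0 = 0.5 to 1.5 over 6 months) and dispersion k = 0.5 to 2.

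**3. Unadjusted precision**

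Var(log RR) = [(1/μ0 + k) + (1/μ1 + k)] / 96.

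Example: 2 falls per year, k = 1, rate ratio 0.7, so μ0 = 1 and μ1 = 0.7.

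- Variance = (2 + 2.429)/96 = 0.0461, so SE = 0.215.
- |log 0.7| / SE = 0.357/0.215 = 1.66.
- Two-sided 5% power = Φ(1.66 − 1.96) ≈ 38%.

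Over 1-3 falls per year and k = 1-2, power at a rate ratio of 0.7 is about 22-45%. For a 10-15% reduction, the size of difference that Sample size mentions for secondary outcomes, it is about 6-17% (k = 0.5-2).

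**4. Analytic gain if a covariate explains a share q of the dispersion**

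Variance ratio, at equal rates in both arms = [1/μ + k(1 − q)] / (1/μ + k).

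- Smallest gain on the grid (1 fall per year, k = 0.5, q = 0.1): (2 + 0.45)/2.5 = 0.98.
- Middle case (2 per year, k = 1, q = 0.5): 1.5/2 = 0.75.
- Largest (3 per year, k = 2, q = 0.5): (0.667 + 1)/(0.667 + 2) = 0.625.

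The variance therefore falls by about 2-38%. In SE terms that is 1 − √0.98 ≈ 1% to 1 − √0.625 ≈ 21%.

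**5. Simulated gain from log(baseline falls + 0.5)**

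Assumed: 96 per arm, 1-3 falls per year, dispersion 1-2, rate ratio 0.7, 12-month history; 400 replicates. Unadjusted power was about 22-48%, in line with step 3.

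| Participants keeping the same underlying fall rate | Cut in SE of log RR | Change in power (points) |
|---|---|---|
| 30% | about 1-2% | −1 to +2 |
| 60% | about 2-9% | −0.5 to +6.5 |
| 100% | about 6-36% | +0.5 to +30 |

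The last row is approximate: up to about 8% of adjusted fits there gave no standard error. With 400 replicates, a power near 50% has a Monte Carlo standard error of √(0.25/400) = 2.5 points. The two models are compared on the same simulated data, which helps, but changes of a point or two should be read as nil.

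A second simulation (2 falls per year, rate ratio 0.65, 300 replicates, persistence defined as the stable share of between-person variation) cut the variance by 4-34%. Power hardly moved at a 50% stable share. It went from 53% to 59% at 75% (dispersion 1) and from 45% to 59% at 100% (dispersion 2).

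**6. Not computed**

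No gain was calculated for baseline SPPB as the covariate.

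**The case against.** The strongest reply is that nothing here is wrong. A negative binomial model with group and an offset is valid under randomisation, the Abstract and Data analysis agree, and an article may leave covariates for a secondary count outcome to an analysis plan that is not shown. Validity stands in full. The last part stands only partly: the article does name covariates outcome by outcome and gives falls none, so this is a stated choice that can be improved, though an unseen plan may already add the term.

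The second reply is that the Outcomes sentence is generic. The same heading covers delivery costs, fidelity and dose delivered, which cannot exist at baseline. That is fair. A reader might infer that a baseline falls count is already in hand and that adjustment is free. The documents do not support this, because no look-back window appears and Data collection mentions only diaries, calendars and facility records. The conditional fix follows from this.

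Third, the SPPB fallback rests on plausibility. The Primary outcome section cites prediction of mortality, nursing home admission and disability, not falls. The intervention table links strength and balance exercise to both mobility and falls, which makes a prognostic role reasonable but does not quantify it.

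Finally, a reader might infer that the omission leaves chance imbalance as a bias. It does not: the confidence interval already allows for chance imbalance, and allocation is stratified by residence.

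**Conclusion.** The point holds as one of efficiency and clarity. The falls model as written uses no baseline information, and a prognostic baseline covariate would normally tighten the rate ratio without changing what is estimated.

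The size is uncertain. Under the assumed rates, dispersion and 12-month history, baseline falls would cut the standard error by about 1-2% with low persistence and 2-9% with moderate persistence. Larger gains need fall-proneness that is nearly fully stable. All of these inputs are assumptions.

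Two stronger readings are not supported. One is that substantial power is being lost: the supported range includes practically none. The other is that falls are the main secondary outcome: they are listed first of four, but the protocol ranks none of them. The case for change is that the potential gain is useful and the simulated downside negligible, about one point of power at worst.

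**What to change.** Before unblinding, state whether falls in a defined pre-randomisation period are recorded.

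- **If they are:** give the look-back window and prespecify the count, for example as log(count + 0.5), as a covariate in the negative binomial model alongside group and the exposure offset.
- **If they are not:** correct the Outcomes statement so that it no longer covers falls, and prespecify baseline SPPB as the covariate instead.

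The cost is one clause in Data analysis. The SPPB option needs no new data. The falls count needs a defined look-back window and is available only if those falls were in fact recorded. If the full analysis plan already contains such a covariate, the article's text only needs to be aligned with it.

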### Patient and public involvement

The rationale, trial design and intervention content were informed by older people receiving aged care services and their advocates, aged care physiotherapists and aged care service providers via several online forums and many formal and informal meetings and conversations. Staff of aged care service provider organisations assisted with recruitment of participants for the research through direct communications within their organisations.

### Governance

The trial will be governed by a project steering committee, consisting of representatives from our aged care partners not directly linked to research activities, an independent consumer advocate and the study investigators. The committee will be chaired by a member of the research team. This committee will facilitate consumer and aged care input into the study, oversee the study protocol and data analysis, support results translation and be involved in the development of the resources at the end of the study period.

## Conclusion

This study addresses the international public health challenge of preventing mobility decline in older people. Deteriorating mobility is common and costly in older people receiving aged care services. The increasing cost of ageing and dementia care services means that there is an economic imperative for governments and service providers to support treatment innovations such as telehealth to ensure that older people have equitable access to appropriate and effective care.^37^ This study is the first known randomised controlled trial to rigorously examine the evidence about the effectiveness, cost-effectiveness and implementation of a telehealth physiotherapy-led exercise programme to improve mobility, reduce falls and improve the quality of life in older people receiving aged care services in their home or residential aged care.

## Data Availability

Data are available upon reasonable request.
